**Exclusion criteria**
Patients aged younger than 18 years.Current or lifetime history of schizophrenia, psychotic disorder, bipolar disorder, or borderline personality disorder.Known history of hypersensitivity or allergy to ketamine-hydrochloride.Current history of dissociative disorders.Current concomitant use of theophylline or aminophylline.Current elevated intracranial pressure.Pregnancy or ongoing breastfeeding in female participants.Concomitant active substance use in the 6 months preceding enrollment (amphetamines, alcohol, and ketamine).Contraindication to receiving ketamine-hydrochloride (eg, current or lifetime history of cerebrovascular accident, current significant hypertension [systolic blood pressure higher than 160 mm Hg in combination with or with an isolated diastolic blood pressure higher than 100 mm Hg], and current severe cardiac decompensation [eg, presence of dyspnea, peripheral edema, elevated jugular venous pressure, hepatomegaly, pulmonary rales, and pleural effusions]).

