### Withdrawal Criteria

A participant will be withdrawn if the participant presents with a severe adverse event or unknown allergic reaction during the first administration of ketamine-hydrochloride or if the participant wants to withdraw from the study for any reason. The participant will receive the necessary treatment to alleviate any untoward events and will be monitored by the study physician until judged appropriate for discharge. Participants will be followed up on the following day to ascertain more details on their condition. Data from a participant who has been withdrawn will be collected up to the day following their withdrawal to ensure that the participant has no more complications. If a participant withdraws from the study at any time, the reasons for withdrawal will be collected and documented as a feasibility study outcome.

Since this is a feasibility study without a specific sample size required to analyze any outcome, participants will not be replaced or added.

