### Intervention

#### Intervention Description

Participants will be randomly assigned to one of 3 arms. Arm 1: Ketamine-hydrochloride infusions alone, Arm 2: CBT in combination with MM (CBT/MM), or Arm 3: Ketamine-hydrochloride infusions in combination with CBT/MM.

Ketamine-hydrochloride will be delivered intravenously for patients in Arm 1 and Arm 3. For this study, 1 mg/kg of ketamine intravenous will be dosed by total body weight and administered over 2 hours up to a maximum dose of 100 mg as per our local institutional protocol.

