#### Arm 1: Ketamine-Hydrochloride Infusion Alone

Patients in Arm 1 receiving a ketamine-hydrochloride infusion alone will receive ketamine infusions on weeks 2, 7, and 12 of the study. After the study intervention, participants will have their vital signs and adverse events monitored for one hour. The anesthesia provider will be responsible for assessing the participant before discharge. Participants will not be allowed to drive after the intervention; therefore, measures will be taken to ensure the participant has an adequate plan of transportation (ie, a companion or suitable transportation).

For safety reasons, the anesthesia provider administering the medication will not be blinded. However, the study personnel designated to collect the outcome data will be unaware of the treatment assignment. Patients will not be blinded to their therapy for the purposes of this feasibility study.

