### Outcome Measures

#### Primary Outcome

The primary outcome of this pilot trial is to determine the feasibility of a large-scale multicenter trial. Feasibility outcomes will include the following variables, with all thresholds listed in parentheses:

Recruitment success (with the specific aim of recruiting all necessary patients within the first year of the trial period).Adequate consent rate (>30% of eligible patients consent to participate in the study).Percentage of patients who complete all medication and psychotherapy visits (ie, intervention adherence; >90%).Percentage of patients who withdraw from the study (eg, due to side effects or other reasons; <20%).Percentage of patients with incomplete pain intensity and pain interference data at 1 month and stated or ascribed reason (eg, withdrawal due to side effects, loss of follow-up, or missing data; <10%).Rate of adverse outcomes (ie, 0 serious adverse events).

Based on the result for each primary feasibility outcome, we will determine whether the definitive study is feasible as proposed (ie, all feasibility targets are met), feasible with protocol modifications (modifications specified), or not feasible because feasibility targets could not be met even with protocol modifications. These cutoffs, identified in the parentheses above, will help determine whether protocol changes are required before proceeding with a definitive trial.

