## Results

### Prestudy Screening

Eligible participants will be screened at the Chronic Pain Clinic at St. Michael’s Hospital. Participants diagnosed with chronic neuropathic pain that meet the criteria from the ID pain questionnaire will be approached and asked to consider study participation.

After participants have provided informed consent, they will be asked about their medical comorbidities, psychiatric history as based on the Mini International Neuropsychiatric Interview, history of ketamine hypersensitivity, and concomitant medications to confirm eligibility. If a participant is eligible to participate in the study, the participant will be enrolled in the study, and the study coordinator will book an appointment for the participant’s study intervention.

At this current point, November 1, 2023, the study has not started enrolling and consenting patients.

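### The hypertension exclusion prints no route for isolated systolic pressure: every literal reading requires diastolic pressure above 100 mm Hg, and on the natural reading the 160 mm Hg limit is redundant

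*Protocol article*

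**What the plan says.** The exclusion criteria in Textbox 1 of the protocol article end with a general clause on contraindications to ketamine, illustrated by examples: "Contraindication to receiving ketamine-hydrochloride (eg, current or lifetime history of cerebrovascular accident, current significant hypertension". Significant hypertension is then defined in a bracket: "systolic blood pressure higher than 160 mm Hg in combination with or with an isolated diastolic blood pressure higher than 100 mm Hg". No other part of the article states a blood pressure limit.

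The criterion bears on safety in the arms that receive the drug: "Ketamine-hydrochloride will be delivered intravenously for patients in Arm 1 and Arm 3". In Arm 1 patients "will receive ketamine infusions on weeks 2, 7, and 12 of the study", and Arm 3 follows the same infusion protocol.

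Eligibility is settled before allocation. Table 1 puts the eligibility screen at the screening visit and randomization at week 1. Prestudy Screening describes a review of comorbidities, psychiatric history, "history of ketamine hypersensitivity, and concomitant medications to confirm eligibility".

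**The concern.** A printed systolic figure tells staff that systolic pressure counts toward exclusion. The bracket does not deliver this. It offers two routes to exclusion, a combined one and an isolated one, and the word for isolation is attached only to the diastolic value: "with an isolated diastolic blood pressure higher than 100 mm Hg". Nothing equivalent is printed for systolic pressure.

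What is at stake is consistent screening. A numeric limit exists so that different staff reach the same decision. Someone who applies the bracket as written would class 150/105 as significant hypertension and 185/90 as not. The article says the pilot will inform a larger multicenter trial, and there the same wording could be applied by staff who do not share this clinic's unwritten understanding.

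**Working it through.** The point concerns the logic of a criterion. There is no figure in the plan to reproduce, and no sample-size calculation applies.

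**Inputs**, both from the bracket in Textbox 1: S = systolic above 160 mm Hg; D = diastolic above 100 mm Hg.

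**Readings of the printed words**

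- Reading 1 (natural): combined elevation, or diastolic elevation alone. (S and D) or (D and not S) = D.
- Reading 2 (natural, with isolation read loosely): (S and D) or D = D.
- Reading 3 (strained): systolic elevation is needed throughout, joined to either form of diastolic elevation. S and (D or (D and not S)) = S and D.
- Probable intent, which the words do not state: S or D.

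**Decisions by example** (yes = meets the definition)

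| Blood pressure | Readings 1 and 2 | Reading 3 | Probable intent |
|---|---|---|---|
| 150/90 | no | no | no |
| 150/105 | yes | no | yes |
| 170/105 | yes | yes | yes |
| 170/90 | no | no | yes |
| 185/90 | no | no | yes |
| 210/95 | no | no | yes |

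**What follows**

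1. Readings 1, 2 and 3 all imply D. No literal reading lets systolic pressure count on its own, however high it is.
2. Under Readings 1 and 2 the bracket equals D. Replacing 160 by any other number would change no decision.
3. Under Reading 3 the 160 limit does matter, because 150/105 is no longer caught. That reading works against itself: a diastolic elevation described as isolated cannot occur together with a raised systolic pressure, so one of its two branches is empty.
4. Rewording to S or D keeps every exclusion made under any of the three readings. Relative to Readings 1 and 2, it adds only S without D, that is, systolic above 160 with diastolic at or below 100.

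**The case against.** The strongest reply is that the bracket is not the operative rule. It explains one example in an open list, and the rule is that a contraindication to ketamine excludes. A clinician who judges a patient at 185/90 unfit can exclude that patient under the present text, and one who sees 160 in print would probably apply it. The comorbidity review before enrollment and the presence of an anesthesia provider are further safeguards. The article also condenses a full protocol that is not shown, so the slip may not exist there.

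This stands as a limit on the weight of the point. It does not remove it. Neither safeguard is described with a systolic limit, and the article itself misstates a criterion that it chose to print.

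Three stronger inferences should be resisted.

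- *That the 160 limit has no effect on any reading.* The phrase is garbled, and under Reading 3 the limit matters. Only the absence of an isolated systolic route holds on every literal reading.
- *That a known number of patients is exposed by the wording.* With equal allocation, which the article does not state, the ketamine arms would hold 30 × 2/3 = 20 patients and 20 × 3 = 60 infusions. Those figures count everyone given ketamine. The share of candidates with isolated systolic pressure above 160 mm Hg is not given.
- *That the wording endangers the safety target*, "Rate of adverse outcomes (ie, 0 serious adverse events"). The documents give no event risk for isolated systolic hypertension at the planned dose, and a serious event in any patient would miss that target. The link says nothing specific about this bracket.

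**Conclusion.** The point holds as a minor wording error in a safety criterion. The printed definition of significant hypertension has no route for isolated systolic pressure. On the natural reading it is simply diastolic pressure above 100 mm Hg. A patient at 185/90 falls outside the definition and can be excluded only by judgement.

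A reader might infer that such a patient must be admitted. The documents do not support that, because the open contraindication clause still permits exclusion.

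The criterion screens all candidates, since it is applied before randomization; its safety relevance is to Arms 1 and 3. The number of patients affected cannot be derived. Sample size, allocation, outcomes and analysis are untouched. The plan itself describes "Since this is a feasibility study without a specific sample size required to analyze any outcome, participants will not be replaced or added", so no power argument arises.

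The conclusion rests on the printed text alone. That the intended rule lets either value count by itself is an inference, though the most plausible one, because a printed systolic limit otherwise has little purpose.

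**What to change.** Reword the bracket to: *systolic blood pressure >160 mm Hg and/or diastolic blood pressure >100 mm Hg*. The clinical team should confirm that this is the intended rule, and the full protocol and screening form should be checked for the same phrase.

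The cost is one phrase in the exclusion criteria. The downside is possibly slightly fewer eligible patients. The documents do not give the number, and it would be none if the clinic already excludes these patients by judgement. The article reports that recruitment had not begun as of November 1, 2023, so on its own account the correction could be made before anyone was screened.

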### Withdrawal Criteria

A participant will be withdrawn if the participant presents with a severe adverse event or unknown allergic reaction during the first administration of ketamine-hydrochloride or if the participant wants to withdraw from the study for any reason. The participant will receive the necessary treatment to alleviate any untoward events and will be monitored by the study physician until judged appropriate for discharge. Participants will be followed up on the following day to ascertain more details on their condition. Data from a participant who has been withdrawn will be collected up to the day following their withdrawal to ensure that the participant has no more complications. If a participant withdraws from the study at any time, the reasons for withdrawal will be collected and documented as a feasibility study outcome.

Since this is a feasibility study without a specific sample size required to analyze any outcome, participants will not be replaced or added.

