#### Secondary Outcome

The secondary outcomes chosen for the definitive trial follow consensus recommendations of core domains that should be addressed in studies examining chronic pain. Information will be collected in these domains as part of the pilot trial using survey-based outcome assessments, either in person during study visits or over the telephone by trained research personnel. The following pain score questionnaires will be used:

Pain intensity on an 11-point (0-10) Numeric Rating Scale.Pain interference on the Patient-Reported Outcomes Measurement Information System (PROMIS-PI) scale.Catastrophic thinking about pain, as measured by the Pain Catastrophizing Scale (PCS).Features of depression, as measured by the Patient Health Questionnaire-9 (PHQ-9).Features of anxiety, as measured by the Generalized Anxiety Disorder-7 (GAD-7).Patient Global Impression of Change Scale (PGIC).

Secondary clinical outcomes will include changes relative to baseline assessment in pain intensity and pain interference at week 20 (4 weeks post-completion of treatment; Figure 1). Scores for all outcomes at weeks 2, 7, 12, 16, and 20 will be compared to baseline scores to assess any progressive additive effects between the treatments. For any patients who withdraw before week 20, their last documented responses will be used as a comparison against baseline data. Patients will be allowed to adjust the dosages of other analgesic medications in conjunction with their primary physician. Analgesic medication use and doses will be tracked at the above time points to assess changes over time. Semistructured interviews will be conducted at 2 points within the study period: at weeks 1 and 20 and after the ketamine infusions (Table 1). The interviews will be audio-recorded to ensure the responses are accurately captured. In-person interviews will be recorded with an encrypted device, and phone interviews will be recorded through the Unity Health Zoom (Zoom Video Communications Inc) recording option. The audio recording files will be saved on St. Michael’s Hospital secure and restricted servers, and the files will be labeled by the study number. The recordings will be transcribed by the research team, and after verifying that the transcriptions are accurate, the audio recordings will be destroyed. Questionnaires will be delivered to patients at prespecified time points, as outlined in the study timeline below.

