## Discussion

It is hypothesized that concurrent pharmacotherapy and psychotherapy have combined effects on the analgesic response. In addition to ketamine’s anesthetic-analgesic properties, it also uniquely alters the individual’s level of consciousness at variable doses. Some researchers posit that the therapeutic experience of psychotherapy may be augmented by ketamine’s alteration of conscious awareness [10]. As demonstrated by this systematic review, few studies have examined ketamine-assisted psychotherapy (KAP) for chronic neuropathic pain. RCTs have not been published on this topic. In addition, there appears to be wide variability in the indication, dosage, and patient treatment setting, such that the current literature is inconclusive.

The 3-arm design allows us to compare the feasibility of KAP with ketamine alone and CBT/MM. We will track feasibility outcomes, including recruitment rate and adverse event rate, to estimate the acceptability of this intervention compared to controls. There are also limitations to this study. Due to the participatory nature of CBT/MM, we are unable to blind patients and the research team to patients’ assigned interventions. To mitigate this, the outcome assessors will be blinded to minimize bias, and we will request and report their “best guess” estimate of each patient’s assigned intervention at the end of the study. We also recognize that there may be different patient outcomes based on the mode of CBT/MM delivery. Patients in arm 1 receiving ketamine alone will have no CBT/MM as part of the trial design. Patients assigned to CBT/MM alone (Arm 2) will be receiving their intervention sessions remotely rather than in-person for 16 weeks. Patients in Arm 3 will be receiving ketamine on weeks 2, 7, and 12 and in-person CBT/MM at this time. They will also be involved with remote CBT/MM sessions from weeks 1 to 16 (except for weeks 2,7, and 12). This hybrid intervention will allow us to collect data on the feasibility of in-person versus remote psychotherapy for this patient population.

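### A severe or allergic reaction at the first ketamine infusion forces withdrawal from the study and ends data collection the next day, so later outcomes go unobserved even in participants willing to stay

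*Protocol article*

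**What the plan says.** The Withdrawal Criteria section of the protocol article fixes the rule in three steps.

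- The trigger is mandatory: "A participant will be withdrawn if the participant presents with a severe adverse event or unknown allergic reaction during the first administration" of ketamine. The same section also allows a participant to leave for any reason.
- Observation then ends: "Data from a participant who has been withdrawn will be collected up to the day following their withdrawal". The stated purpose is to confirm that there are no further complications.
- The place is not refilled ("participants will not be replaced or added"), although "the reasons for withdrawal will be collected and documented as a feasibility study outcome".

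The first infusion is at week 2 (Arm 1 description and Table 1). The secondary clinical outcomes are "changes relative to baseline assessment in pain intensity and pain interference at week 20". For anyone who withdraws before then, the Secondary Outcome section compares the last documented response with baseline.

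Two primary feasibility measures count such cases. One is "Percentage of patients who withdraw from the study (eg, due to side effects or other reasons; <20" percent). The other is "Percentage of patients with incomplete pain intensity and pain interference data at 1 month and stated or ascribed reason", with a limit of 10%, and it names withdrawal for side effects among the reasons.

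**The concern.** Stopping a drug and leaving a study are different events. Here the first forces the second. A participant who reacts badly at week 2 must stop ketamine, but nothing in that reaction prevents a telephone questionnaire at week 20. The article nowhere provides for stopping infusions while remaining in follow-up.

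Three things are at stake:

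- **Safety capture.** The people who reacted are the ones whose scheduled adverse-event records stop.
- **Week 20 estimates.** The forced loss depends on arm and on reaction to treatment. A score from week 2 or earlier replaces the one meant to show whether any benefit lasts.
- **The incomplete-data measure.** It would partly record the protocol's own rule instead of participants' willingness to keep answering.

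**Working it through.** The plan gives no figure on this point, so there is none to reproduce. The check is a count of what one triggered case loses.

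**Inputs**

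- Questionnaires: weeks 1, 2, 7, 12, 16 and 20; adverse events: weeks 2, 7, 12, 16 and 20 (Table 1).
- Infusions: weeks 2, 7 and 12, Arms 1 and 3 only (Table 1).
- Remote CBT/MM in Arm 3: "They will also be involved with remote CBT/MM sessions from weeks 1 to 16 (except for weeks 2,7, and 12"; those three weeks are in person (Discussion).
- Total sample: 30 (Aim). The allocation ratio is not stated.

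**Loss per case, exit one day after the week 2 infusion**

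- Questionnaires after baseline: 5 scheduled, at most week 2 kept, 4 of 5 lost (weeks 7, 12, 16, 20).
- Adverse-event visits: 5 scheduled, week 2 kept, 4 of 5 lost.
- Unobserved time: weeks 3 to 20 = 18 of 20 weeks.
- CBT/MM in Arm 3: weeks 3 to 16 = 14 weeks; minus weeks 7 and 12 leaves 12 remote weeks with no infusion.

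**What replaces week 20.** The last documented response comes from week 2 or earlier. It precedes the second and third infusions and nearly all of the psychotherapy. If only the baseline questionnaire was completed, the change is zero by construction. Outcome Analysis separately says that data will not be extrapolated for missed sessions or incomplete questionnaires. Under either rule no observed week 20 score exists.

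**Feasibility measures, denominator 30**

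| Cases | Share of 30 | Incomplete data (<10%) | Withdrawal (<20%) |
|---|---|---|---|
| 1 | 3.3% | within | within |
| 2 | 6.7% | within | within |
| 3 | 10.0% | limit reached | within |
| 6 | 20.0% | limit reached | limit reached |

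These rows count forced withdrawals alone. The 1-month time point for incomplete data falls after the exit whether it is counted from the start of treatment or from its end.

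If the arms were equal at 10 each, one case would be 1/10 = 10% of an arm's observed week 20 scores.

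**Illustration of frequency.** The documents give no reaction rate. Assume 20 of 30 participants are exposed and an unknown rate p. The chance of at least one case is 1 − (1 − p)^20; the chance of three or more is the upper tail of a binomial distribution with n = 20.

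| Assumed p | Expected cases | At least 1 | 3 or more |
|---|---|---|---|
| 2% | 0.4 | 33% | 0.7% |
| 5% | 1 | 64% | 7.5% |
| 10% | 2 | 88% | 32% |
| 15% | 3 | 96% | 60% |

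The table shows only how strongly the answer depends on p; it is not a prediction.

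**The case against.** The strongest reply is that this is a rare contingency in a small pilot. The trigger covers the first infusion only, known ketamine hypersensitivity and listed contraindications are excluded, and the dose is capped at 100 mg over 2 hours. The pain outcomes are secondary and unpowered. All of this stands, and it limits the weight of the point.

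Four stronger readings are tempting, and the documents do not support them.

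- *The participant drops out of the week 20 comparison.* The Secondary Outcome section carries the last response into a comparison with baseline. The problem is that this response is too early to show durability.
- *Counting these cases as withdrawals distorts feasibility.* The Primary Outcome section includes side effects by design, and reasons are documented. A severe first reaction is something a pilot should count. Removing such cases from the withdrawal measure would redefine it.
- *Safety is neglected.* The Withdrawal Criteria provide treatment, physician monitoring until discharge and a next-day contact. The full protocol may also contain safety follow-up that the article condenses. What can be said is that the article's stated rule ends the scheduled adverse-event records.
- *The rule makes the pilot fail.* One or two cases alone breach neither percentage limit. If a reaction were classed as serious, the target of zero serious adverse events would be missed whatever the follow-up.

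The cutoff could also be read as covering safety data only, given its stated purpose. The sentence does not restrict the data it covers, however, and the last-response rule implies that no later scores are expected. The narrow reading is therefore unlikely, and a clarifying sentence would settle it.

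**Conclusion.** The point holds in limited form. The article states a rule that joins stopping ketamine to leaving the study and ends data collection a day later, even for participants willing to continue. From this trigger, only Arms 1 and 3 are affected. Each case costs 4 of 5 post-baseline questionnaire visits, 4 of 5 scheduled adverse-event records and 3.3 points on the incomplete-data measure, and leaves a response from week 2 or earlier in place of week 20.

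The visit counts follow from Table 1 without assumptions. The 10% share of an arm assumes equal arms of 10, and no event rate is known. A reader might infer that the rule biases an efficacy conclusion. The article plans no powered efficacy conclusion, so the effect stops at safety capture, the incomplete-data measure and descriptive estimates. Voluntary withdrawal falls under the same next-day cutoff, but ending follow-up there is easier to understand and is not the point here. Reactions at weeks 7 and 12 are not covered by the mandatory trigger.

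**What to change.** Change the Withdrawal Criteria as follows.

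1. After a severe adverse event or unknown allergy at the first infusion, stop study infusions and keep the participant in the study. Continue scheduled questionnaires and adverse-event recording to week 20 unless consent is withdrawn. The blinded assessor can take the questionnaires by telephone, and unblinded staff can record adverse events, which fits the Follow-Up Data and Blinding Mechanism sections.
2. Use the observed week 20 scores of these participants instead of the last documented response.
3. Report two separate counts: stopped ketamine because of side effects, and left follow-up. Keep the first within the existing withdrawal measure so that side-effect discontinuations stay visible.
4. Optionally, let Arm 3 participants continue CBT/MM at clinical discretion. They would no longer be receiving the combination that the arm tests, and should be described accordingly.

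The cost is protocol wording and at most four already scheduled contacts (weeks 7, 12, 16 and 20) per affected participant, some of whom may decline. The 3.3 points on the incomplete-data measure are recovered only for those who stay and complete the questionnaires. The withdrawal measure, the adherence measure (a stopped infusion still counts as 1/30) and the serious adverse event target are unchanged. Recruitment had not begun at the article's status date of November 1, 2023.
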